#### Health literacy

Health literacy will be measured with HLS-Q12 which is a short version of the European Health Literacy Survey Questionnaire [24]. Health literacy can be defined as an individual’s cognitive and social skills which determine motivation and ability to gain access to, understand and to use information in such a way that promote and maintain good health [25]. Health literacy is believed to have a vital impact on public health, and low health literacy has been related to unhealthy behaviors [26].

#### Self-perceived goal achievement

Self-perceived goal achievement for each goal, decided by the participant at baseline, will be assessed on a Likert-scale (0–100, where 0 represent far away from reaching the goal and 100 that the goal has been reached).

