### Intervention group

The intervention that will be delivered is individualized follow-up enabled by a smartphone-app. The app that will be used was developed to guide and help individuals to change behavior and/or to maintain habits. It permits the app-user to create and set goals (Fig. 2) with tasks and accompanying reminders. A supervisor has access to an administrator interface (Fig. 3) and may monitor the goals and tasks of each app-user. In addition, the app-user can write reflections in the app that the supervisor may read in the administrator interface. The app itself provides reminders and evaluations of tasks and weekly goal achievement that automatically pop up. In these evaluations, the app-user has to reply with a red or green face depending on whether they have completed the planned tasks or not, in addition to score on a Likert-scale (0–100) to evaluate the weekly goal achievement.

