**Fig. 3 Fig3:**
[figure not shown]
Administrator interface, showing one goal with related tasks

At baseline, a supervisor will guide each participant in setting individual goals by using elements from motivational interview. Each participant will be encouraged to set a minimum of one goal, with corresponding achievable tasks to reach the goal(s). Further, they will receive access to the app, as well as guidance in how to use it. The participant will decide when and how often reminders of the tasks should appear on their smartphone. The lower limit of amount of reminders will be one reminder each week for each task. There will not be any upper limit. During the follow-up period, the participants will receive short, tailored and individualized motivational feedback directly through the app, one to three times a week, as well as comprehensive individual feedback through e-mail once a week for the first 12 weeks, and every fourth week rest of the year. All individual feedback will be given based on what the participants have done, not done and/or their reflection notes. Participants can submit questions to the supervisor at any time, receiving an answer within two working days throughout the year. If the questions are medically related (e.g. changing medication or chest pain), they will be advised to contact their general practitioner. The participants will be monitored and followed for 12 months, by the same supervisor that includes the participants at baseline. The follow-up will be given regardless of whether the participant has used the app. In such cases, the feedback is likely to be of a more general nature.

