### Control group

Participants allocated to the control group will receive treatment as usual. As a part of the baseline assessment, the researcher will guide each participant in setting individual goals by using elements from motivational interview. They will be encouraged to maintain or improve their current physical activity level, exercise habits and/or a heart healthy diet, depending on their own goals and needs. They will be contacted approximately five weeks before their follow-up assessment at 12 months.

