### Outcomes

The primary outcome measure will be change in VO_2peak_. Secondary outcome measures will include exercise performance, QoL, health status, health literacy, self-perceived goal achievement, exercise habits, body weight, blood pressure, lipids and triglycerides.

All assessments will be performed at baseline and at 12 months. Outcome measures will be conducted at the same CR center as the participants were attending CR. At baseline, when the participants complete their CR, demographic data, including individual goals for the next year, will be collected. The assessments will be administrated in a standardized way, which means that all assessments for each participant will be carried out in the same order.

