### Statistical procedures

The results of the study will be reported in accordance to CONSORT statement [27]. Statistical analysis will be performed using SPSS or a similar statistical package. Descriptive data will be reported for variables of interest and will be reported as mean (standard deviation), median (range) or numbers (percent) as appropriate. The data will be analyzed following the intention-to-treat principle. Prospective differences in primary and secondary outcomes and baseline characteristics between the intervention group and the control group will be assessed by t-tests for continuous and normally distributed variables and with non-parametric tests for categorical variables. To control for confounding of between group differences, multiple linear regression modelling will be used. We expect few or none missing data in baseline characteristics. However, due to possible dropouts or participants unable to complete some of the outcome measurements, there might be missing data for both primary and secondary outcome measures at follow-up. Missing data will be assessed and analyzed with appropriate methods. All tests will be two-sided. A plan for statistical analysis will be performed in advance of each paper from the study.

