## Discussion

To our knowledge, this will be the first study to examine the effects of one-year individualized follow-up with an app after completed CR, aiming to promote adherence to lifestyle advice. We anticipate that the intervention described will have a positive impact on the primary outcome, VO_2peak_, as well as secondary outcomes such as exercise performance, body weight, QoL and self-perceived goal achievement. If the intervention proves to be effective, we will be able to support participants in the intervention group to adhere to lifestyle advice and thereby maintain the beneficial effects they have achieved in CR, which has proven to be difficult for the patient population several times [5, 32, 33]. Additionally, by evaluating the impact of the intervention, we hope to contribute to fill the knowledge gap that has been addressed by previous research in the field [3, 6, 9, 12, 34], and it is reasonable to assume that the study may be groundbreaking. Due to the large sample size and the theoretically based intervention, the study has the potential to generate new knowledge that may improve the design of future technology-based follow-up interventions of patients that have completed rehabilitation.

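### Self-perceived goal achievement mixes goals that can rise with goals that may start at the ceiling; compare 12-month levels adjusted for baseline score and goal type, and do not use a change score

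*Protocol article*

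**What the plan says.** - **Outcome.** The section on self-perceived goal achievement states: "Self-perceived goal achievement for each goal, decided by the participant at baseline, will be assessed on a Likert-scale". The anchors are "0–100, where 0 represent far away from reaching the goal and 100 that the goal has been reached".
- **Timing.** The Outcomes section states: "All assessments will be performed at baseline and at 12 months". A baseline and a 12-month rating are therefore scheduled. That section uses the word change for peak oxygen uptake but not for goal achievement.
- **Number of goals.** The Intervention group section states: "Each participant will be encouraged to set a minimum of one goal, with corresponding achievable tasks to reach the goal(s"). No maximum is given.
- **Kind of goal.** Under Control group, participants are "encouraged to maintain or improve their current physical activity level", depending on their own goals and needs. The Intervention group section describes the app as serving both behaviour change and the keeping of habits.
- **Weekly rating.** The same section has app users give a 0–100 score "to evaluate the weekly goal achievement". Only the intervention arm has the app, for 12 months.
- **Analysis.** Under Statistical procedures, prospective differences in primary and secondary outcomes "will be assessed by t-tests for continuous and normally distributed variables". Non-parametric tests are named for categorical variables. Multiple linear regression is added to control for confounding, with no covariates named. A separate analysis plan is to precede each paper.
- **Expectation.** The Discussion anticipates a positive effect on the primary outcome "as well as secondary outcomes such as exercise performance, body weight, QoL and self-perceived goal achievement".

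**The concern.** The scale measures distance to a self-chosen goal, and the goals are of two kinds. Someone who wants to walk more than now starts well below 100 and has room to rise. Someone who wants to keep a habit gained in rehabilitation may rate the goal as reached, or nearly so, on day one.

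This matters for the choice of summary. On a change score, a maintenance goal kept for the whole year scores about 0, the same as an improvement goal on which nothing happened. Goal type then adds a large spread that has nothing to do with treatment. An unadjusted comparison of 12-month levels suffers far less, but still leaves that spread in the error term. The article does not say which of the two is meant for this outcome.

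There is also a point of interpretation. For a year, one arm is prompted every week to rate its goal achievement from 0 to 100, and the other is not. Participants know their allocation, and the blinding described covers only the assessors of the primary outcome, who also measure blood pressure. Repeated rating could make the app arm more generous or more severe with the scale, apart from any real progress.

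**Working it through.** **Plan's own figure.** None is given for goal achievement. The only one is 47 per group for peak oxygen uptake, and it reproduces: 2 × (1.960 + 0.842)² × (6/3.5)² = 2 × 7.85 × 2.94 = 46.1, rounded up to 47. I use 47 per arm below.

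**Assumed inputs** (the article gives no goal scores):
- one score per participant;
- 12-month control mean 60 for improvement goals and 75 for maintenance goals, SD 25 within each type;
- baseline 100 for maintenance goals; mean 30, SD 25 for improvement goals;
- no correlation between baseline and 12 months within a goal type;
- true benefit 15 points before scores are limited to 0–100;
- two-sided 5% t-test.

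**Closed form, ignoring the limits.** Let p be the share of maintenance goals. The mean change is 75 − 100 = −25 for maintenance and 60 − 30 = +30 for improvement, a gap of 55.
- Variance of the 12-month level: 625 + p(1 − p) × 15². At p = 0.5 this is 681.25, SD 26.1.
- Variance of the change: p × 625 + (1 − p) × 1250 + p(1 − p) × 55². At p = 0.5 this is 937.5 + 756.25 = 1693.75, SD 41.2.
- Relative efficiency of the change score: 681.25/1693.75 = 0.40.
- With √(2/47) = 0.206, the standardised effect is 15/(26.1 × 0.206) = 2.79 on levels and 15/(41.2 × 0.206) = 1.77 on change. Power is Φ(2.79 − 1.96) = 0.80 and Φ(1.77 − 1.96) = 0.42.

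**Simulation with scores limited to 0–100** (2,000 trials per cell). The limit shrinks the 15-point benefit, to about 12.4–12.8 points at p = 0.5, so power is somewhat lower.

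| Share of maintenance goals | Power, 12-month level | Power, change |
|---|---|---|
| 0% | 0.83 | 0.53 |
| 25% | 0.79 | 0.37 |
| 50% | 0.76 | 0.35 |
| 75% | 0.78 | 0.39 |
| 100% | 0.76 | 0.76 |

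**How much is due to mixing.** The 0% row shows that part of the loss comes from the assumed zero correlation within improvement goals, since 0.83 falls to 0.53 with no mixing at all. If that correlation were 0.5, the improvement-goal change variance would be 2 × 625 × (1 − 0.5) = 625. At p = 0.5 the total is then 625 + 756.25 = 1381.25, and relative efficiency is 681.25/1381.25 = 0.49. The change score still discards about half the information.

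**What adjustment adds to the 12-month level.** Taking out goal type lowers the variance at p = 0.5 from 681.25 to 625, a ratio of 0.92. A baseline score correlated r with the outcome within goal type lowers it further by the factor 1 − r². The gain over an unadjusted comparison of levels is modest; the large gain is in avoiding the change score.

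**A shift in scale use** (same simulation, 12-month levels). The size and direction are unknown, so these are illustrations only.
- No true benefit, app arm's ratings shifted by 5 points: a significant difference favouring the app arm in about 14–16% of trials, against 2.5% nominal in that direction.
- No true benefit, shifted by 10 points: about 42–49%.
- True 15-point benefit, ratings shifted by −10 points: power falls to about 0.15–0.16.

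**The case against.** The strongest reply is that the article commits to none of the harmful choices. It specifies no change score for this outcome, it names multiple linear regression alongside the t-test, and it announces an analysis plan before each paper. That is fair: the proposed model is compatible with the text. What stands is that the t-test is the stated between-group comparison, that prospective differences can be read as change, and that nothing alerts the analyst to the mixed scale.

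A second reply is that a ceiling at baseline is inferred. No baseline scores or share of maintenance goals are given. The goals are for the coming year, so a participant may not rate a maintenance goal as already reached. This stands as well, which is why the point is worded as may start near 100. Randomisation also makes goal type a source of noise, not of systematic bias.

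On the weekly rating, three stronger readings are tempting and unsupported:
- A reader might take it for the outcome instrument itself. The article gives the 0–100 range for weekly achievement but no anchors.
- A reader might infer that the supervisor responds to the weekly score. The text has the supervisor monitoring goals and tasks and reading reflections, with feedback based on what was done, not done or noted.
- A reader might count a full year of weekly ratings. The article itself plans for participants who stop using the app.

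What remains is the asymmetry in prompted ratings, in an unblinded trial.

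**Conclusion.** The concern holds as a matter of analysis choice and reporting for one secondary outcome. Under the stated assumptions with 25–75% maintenance goals, a change-score t-test has power of about 0.35–0.39, where a comparison of 12-month levels has 0.76–0.79. The loss depends on the assumed goal mix, baseline scores and correlation, and it vanishes if all goals are maintenance goals starting at 100. Adjusting the 12-month level for baseline score and goal type is at least as precise as the unadjusted comparison, apart from a negligible loss of degrees of freedom.

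Three stronger conclusions do not follow:
- The test is not incapable of showing benefit. If controls lapse from maintenance goals their scores fall, and power on 12-month levels is 0.76–0.83 throughout the table.
- The article does not say that several goals from one person enter the test as independent values. How they are combined may properly be left to the analysis plan.
- The outcome need not become descriptive only, and the Discussion's anticipated benefit is a hypothesis that may stand. The one-arm rating calls for a stated caution, because the documents give neither the size nor the direction of any shift.

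**What to change.** In the analysis plan for the paper that reports this outcome:
1. Define one value per participant: the mean 12-month score over the goals set at baseline.
2. Compare arms by linear regression of that value on arm, with the mean baseline score over the same goals and goal type (maintain or improve) as covariates. For a participant with both kinds, use the share of goals that are maintenance goals.
3. Code goal type from the goals recorded at baseline, before any unblinded analysis and without knowledge of arm.
4. State that no change score will be used for this outcome.
5. When reporting, note that only the intervention arm was prompted for a weekly 0–100 goal rating and that participants were unblinded, so a difference in either direction may partly reflect a shift in use of the scale.

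The cost is a few sentences and one simple coding of each goal. No new data are needed: the goals and both ratings are already scheduled. Sample size and the primary analysis do not change.

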#### Exercise habits

Exercise habits will be assessed through the standardized consultation and will be defined as mean exercise sessions each week for the last year. In this context, an exercise session is defined as structured activity lasting at least 30 min where you get both sweaty and breathless, and you feel like taking a shower afterwards.

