### Study setting and recruitment

Participants will be recruited from two CR centers in the eastern part of Norway. One rehabilitation center offers a outpatient CR program for 12 weeks, while the other center offers two inpatient CR programs, one and four weeks respectively. Approximately one third of the participants will be recruited from each of the three CR programs. A researcher will visit the CR centers on a regular basis to conduct the recruitment. During CR, all patients will receive information about the study orally, as well as a request of whether they have interest in taking part in the study. If the participants are willing and able to participate in the study, they will get an appointment for baseline assessment at the time they complete the CR program. Prior to baseline assessment, the participants must provide a written informed consent. Figure 1 presents the planned flow of participants in the study.

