### Randomization

Participants will be randomly assigned at a 1:1 ratio in variable blocks to the intervention group and the control group. The randomization will be stratified to ensure equal numbers of participants from the three different CR programs in the intervention- and control group, respectively. A computer-generated, permuted block randomization scheme will be used to allocate the participants. To minimize bias, and to optimize the rigor of the RCT, a number of methodological factors have been incorporated into the design of the study. Participants will be randomly allocated to the groups via concealed allocation. Due to the nature of the intervention, it is impossible to blind the participants, nor the supervisor giving the follow-up, to the allocated groups. However, assessors for primary outcome measure will be blinded to the allocated groups. Further, intention-to-treat analyzes will be conducted to reduce bias. This maintains the random assignment to the groups and imitate the real-life situation.

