#### Blood pressure

The assessor of the primary outcome (blinded for group allocation) will also measure blood pressure prior to the CPET. Measurement will be done manually, preferably on the left arm. Participants will be sitting on a chair relaxing for 3–5 min before measurements will be done. Three measurements will be performed, of which the lowest measured value will be used.

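### Exercise habits are a one-year self-report in a consultation outside the stated blinding, so the group difference is open to reporting bias; change from the baseline year cannot be read as maintenance

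*Protocol article*

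**What the plan says.** All references are to the protocol article.

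- **Measurement (Exercise habits).** "Exercise habits will be assessed through the standardized consultation and will be defined as mean exercise sessions each week for the last year". What counts as a session depends partly on how it felt: "an exercise session is defined as structured activity lasting at least 30 min where you get both sweaty and breathless".
- **Blinding (Randomization).** The blinding statement is that "assessors for primary outcome measure will be blinded to the allocated groups". The same section says that "it is impossible to blind the participants, nor the supervisor giving the follow-up, to the allocated groups".
- **Blinding (Blood pressure).** The blinded role is widened once: "The assessor of the primary outcome (blinded for group allocation) will also measure blood pressure prior to the CPET". No section widens it to the consultation.
- **Contact during the year (Intervention group).** Feedback comes through the app one to three times a week, with e-mail feedback in addition, and draws on tasks done or not done and on the participant's notes. Of the staff member, the section says: "The participants will be monitored and followed for 12 months, by the same supervisor that includes the participants at baseline".
- **Contact during the year (Control group).** Goals are set at baseline as well, and the next contact described is about five weeks before the 12-month visit.
- **Timing (Outcomes).** Baseline is when CR ends, and assessments are repeated at 12 months. The word change is attached only to peak oxygen uptake.
- **Programmes (Study setting and recruitment).** One centre runs an "outpatient CR program for 12 weeks, while the other center offers two inpatient CR programs, one and four weeks respectively". About a third of participants come from each programme, and randomisation is stratified by programme.
- **Analysis (Statistical procedures).** Primary and secondary outcomes are compared between groups by t-tests or non-parametric tests, with multiple linear regression to control for confounding.

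**The concern.** Exercise habits are the only listed outcome that directly measures exercise behaviour, which is what the app is meant to sustain. The answer is subjective and given by people who know their allocation. One arm has spent the year rating its tasks and reading feedback on them, which can both aid recall and encourage a favourable answer. Randomisation does not protect against this, because the distortion arises after allocation. Baseline adjustment does not remove it for the same reason.

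The second issue is what the baseline value means. The Discussion describes the goal as keeping the gains made in CR. A reader who sees baseline and 12-month values side by side will naturally take the difference as habits kept or lost since CR. The baseline window does not support that reading.

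**Working it through.** No figure in the protocol needs reproducing for this point. The check has two parts.

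**1. Who is blinded to what**

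| Item | Source of the value | Stated blinding |
|---|---|---|
| Peak oxygen uptake | Measured by assessor | Assessor blinded |
| Blood pressure | Measured by the same assessor | Assessor blinded |
| Exercise habits | Participant's recall, in a consultation | None stated for the consultation; participant unblinded |

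Write b_I and b_C for the mean over-reporting in sessions per week in the intervention and control arms. Then:

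observed difference = true difference + (b_I − b_C)

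Equal over-reporting cancels; unequal over-reporting does not. The documents give no value for b_I − b_C. If it were 0.25 to 0.5 sessions per week (an assumption, for illustration only), a true difference of 0 would appear as 0.25 to 0.5.

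**2. What the baseline year contains**

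Inputs: programme length w = 1, 4 or 12 weeks (Study setting and recruitment); window of 52 weeks (Exercise habits); baseline when CR ends (Outcomes).

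Share of the window in CR = w/52:

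- 1 week: 1/52 = 1.9%, leaving 98.1% before CR
- 4 weeks: 4/52 = 7.7%, leaving 92.3%
- 12 weeks: 12/52 = 23.1%, leaving 76.9%
- average with one third each: (1 + 4 + 12)/3/52 = 10.9%

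To see the effect on a change score, let p be sessions per week before CR and c during CR. Neither is in the documents.

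baseline value = (w·c + (52 − w)·p)/52

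For someone who keeps rate c throughout follow-up:

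apparent change = c − baseline value = (c − p)(52 − w)/52

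With p = 1 and c = 3 (assumed):

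| Programme | Baseline value | Apparent change |
|---|---|---|
| 1 week | (3 + 51)/52 = 1.04 | +1.96 |
| 4 weeks | (12 + 48)/52 = 1.15 | +1.85 |
| 12 weeks | (36 + 40)/52 = 1.46 | +1.54 |

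Over assumed ranges of 0 to 2 for p and 2 to 5 for c, the apparent change runs from 0 (p = c = 2) to +4.9 (p = 0, c = 5, 1-week programme). Relative to the end of CR, the true change is 0 in every case. Unless p equals c, a person who fully maintains the CR level looks like an improver, by an amount that depends on the programme.

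The window at 12 months has no such problem: it covers the follow-up year, which is the intervention period.

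**The case against.** Several points on the other side are sound.

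- **The interviewer is not named.** A reader might infer that participants report to the supervisor who coached them. The text says who includes and follows intervention participants, not who takes the history at 12 months. A condensed article may leave that to the full protocol, so the silence is not itself an error. The concern does not depend on it: participants are unblinded whoever asks.
- **No change score is planned for this outcome.** A reader might infer one from the two assessment times. The article does not state it, and comparing 12-month values between groups is consistent with the text.
- **The mixed baseline does not bias the arms.** A reader might take the 2%, 8% and 23% shares as a source of bias in the trial result. They differ between programmes, and stratification balances programmes across arms. The effect is on interpretation and precision.
- **Feedback need not concern exercise.** It follows each participant's own goals, and the control-group text mentions diet too. The differential prompt will therefore be stronger for some participants than for others.
- **Some obvious remedies have costs.** If the exercise-test assessor took the history, a participant could mention the app and unblind the primary outcome. A 3-month window would miss nine months of the intervention. The reminder sent five weeks ahead would also fill 5/13 = 38% of it, against 5/52 = 10% of the year.

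What remains is that a subjective recall, from unblinded participants with unequal prompting, is collected in a setting outside the stated blinding. No later analysis can repair that.

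**Conclusion.** The point stands in two limited parts.

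1. The group difference in exercise habits is open to reporting bias, most plausibly in favour of the intervention. Its size cannot be derived from the documents; whatever it is passes unchanged into the difference. This rests only on the stated mode of collection, the stated scope of blinding and the unequal contact between arms.
2. Any change from baseline should not be read as maintenance of end-of-CR habits, because 77% to 98% of the baseline year precedes CR. The shares follow from the programme lengths; the session rates used to illustrate the consequence are assumed. This part concerns meaning, not bias in the randomised comparison.

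The outcome is secondary. The primary outcome is measured by a blinded assessor, and its conclusion is not affected.

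**What to change.** - At the 12-month visit, collect exercise habits on a self-completed form, with the session definition printed on it, before any contact with the supervisor or other unblinded staff. Do the same for the goal-achievement scores, which are also self-rated. Do not route either through the exercise-test assessor.
- Keep the one-year window, since at 12 months it matches the follow-up year.
- State that 12-month values are compared between groups by linear regression adjusted for the baseline value and CR programme, in place of an unadjusted t-test and not as change from baseline.
- Say in the report that self-report bias from unblinded participants remains, and that the baseline year mostly precedes CR.

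The cost is a short form and a change in visit order, with no extra staff. The downside is slightly less interviewer help in applying the session definition. The form reduces the influence of an unblinded interviewer; it does not remove over-reporting by participants who know their allocation.
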